## Abstract

**Background:**

General anesthesia in pregnant women can be associated with significant maternal and fetal morbidity. Emergency caesarean section can be performed by converting labor epidural analgesia to surgical anesthesia by injecting high-dose short-acting local anesthetics through the epidural catheter. The effectiveness and the delay to obtain surgical anesthesia depends upon the protocol used. Data indicate that alkalinization of local anesthetics may shorten their onset of action and increase their effectiveness. This study investigates whether alkalinization of adrenalized lidocaine could increase the efficacy and decrease the delay of onset of surgical anesthesia via an indwelling epidural catheter, thus decreasing the necessity to resort to general anesthesia for emergency caesarean deliveries.

**Methods:**

This study will be a bicentric, double-blind, randomized, controlled trial with two parallel groups of 66 women who require emergency caesarian deliveries and who have been receiving epidural labor analgesia. The number of subjects in groups will be unbalanced with a 2:1 ratio of experimental:control. In both groups, all eligible patients will have had an epidural catheter placed for labor analgesia with levobupicaine or ropivacaine. Patient randomization will occur when the decision is made by the surgeon that an emergency caesarean delivery is indicated. Surgical anesthesia will be obtained by injecting 20 mL of 2% lidocaine with epinephrine 1:200,000, or 10 mL 2% lidocaine with epinephrine 1:200,000 plus 2 mL sodium bicarbonate 4.2% (total of 12 mL). The primary outcome will be the rate of conversion to general anesthesia for failure of the epidural to provide adequate analgesia. This study will be powered to detect a 50% reduction in the incidence of general anesthesia, from 80 to 40%, with a confidence ratio of 90%.

**Discussion:**

Sodium bicarbonate could be used to avoid general anesthesia for emergency caesarean deliveries by providing reliable and effective surgical anesthesia in women with pre-existing labor epidural catheters is promising. This randomized controlled trial seeks to determine the optimal local anesthetic mixture for converting epidural analgesia to surgical anesthesia for emergency caesarean sections. This may decrease the need for general anesthesia for emergency caesarian section, shorten the time to fetal extraction, and improve safety and patient satisfaction.

**Trial registration:**

ClinicalTrials.gov NCT05313256. Registered on 6 April 2022

**Supplementary Information:**

The online version contains supplementary material available at 10.1186/s13063-023-07366-1.

## Administrative information

Note: the numbers in curly brackets in this protocol refer to SPIRIT checklist item numbers. The order of the items has been modified to group similar items (see http://www.equator-network.org/reporting-guidelines/spirit-2013-statement-defining-standard-protocol-items-for-clinical-trials/*).*

## Introduction

### Background and rationale {6a}

Epidural analgesia is performed throughout the world for intrapartum pain relief. Approximately 85% of women in France use epidurals during labor [1]. In the case of emergency caesarean section, surgical anesthesia can be obtained by injection of a rapid-onset local anesthetic (LA) via an existing epidural catheter. If insufficient analgesia is obtained by this method, the patient must receive a general anesthetic. General anesthesia for emergency caesarean delivery is associated with significant maternal and fetal morbidity, including a higher incidence of difficult oro-tracheal intubation [2, 3], aspiration of gastric contents [4], and neonatal respiratory depression [5].

The French Society of Anesthesia and Intensive Care Medicine (Société Française d’Anesthésie et de Réanimation, SFAR) [6] provides guidelines for the use of an epidural catheter that has been placed for labor analgesia to convert to surgical anesthesia (“epidural conversion”) for emergency caesarean deliveries with the addition of 15 to 20 ml of 2% lidocaine plus adrenaline 1:200,000 to an existing epidural. The onset of surgical anesthesia is usually seen within 10 to 15 min. In cases of insufficient analgesia, general anesthesia will be required. Therefore, the key to avoiding a general anesthetic in this population is the rapid and predictable onset of surgical anesthesia via an indwelling epidural catheter.

The addition of sodium bicarbonate to commercially available lidocaine increases its pH towards the physiological range. Theoretically, this would enhance the speed of onset of a lidocaine nerve block, but this effect remains controversial in animal models and in clinical practice. In preparations of rat sciatic nerve, the effect of lidocaine was enhanced in the presence of a carbon dioxide-rich microenvironment [7]. In clinical practice, however, the addition of sodium bicarbonate to lidocaine is used in 35% of labor epidural conversions to surgical anesthesia in Denmark [8] and in 12% of epidural conversions in the UK [9]. Although clinical studies have shown the efficacy of this technique in scheduled caesarean sections [10–12], only two randomized, controlled trials have been conducted specifically in the context of emergency caesarean delivery during labor. In the first [13], the addition of 1.2 ml 8.4% sodium bicarbonate to a mixture of 15 ml 2% lidocaine with epinephrine 1:200,000 plus fentanyl 75 μg decreased the delay required to obtain a T6 epidural anesthesia by 50% (5.2 min vs. 9.7 min [*p* < 0.001]), without maternal or fetal adverse effects. In the second study [14], a mixture of 1.8% lidocaine with epinephrine 1:200,000 plus 0.76% bicarbonate was compared to levobupivacaine. The onset of T5 block (bilateral sensory block to touch at the T5 dermatome level) was shorter in the epidural mixture group. More recently, Reschke et al.’s 2019 meta-analysis examined the six most commonly used epidural extension solutions across 1280 patients in 24 randomized controlled trials. Using a network Bayesian analysis of time to epidural anesthesia, the authors found lidocaine 2% alkalinized with bicarbonate as the top-ranking solution for speed of epidural anesthesia [15].

The main hypothesis to explain this pharmacokinetic effect is that lidocaine molecules exist in a greater proportion of its non-ionized form in an alkaline environment. The non-ionized form is the only one capable of crossing the perineural membrane and inducing a conduction block of sodium channels [16].

For emergency caesarean delivery, there are many combinations that can be used with 2% lidocaine. In our unit, we mainly use two combinations, according to the choice of the practitioner: 20 ml of 2% lidocaine with epinephrine 1:200,000 or a 12 mL mixture of lidocaine plus bicarbonate (10 mL of 2% lidocaine with epinephrine 1:200,000 plus 2 mL 4.2% sodium bicarbonate ). This last combination was adopted as a result of previous preliminary studies that showed rapidly established surgical anesthesia. However, the incidence of failure to achieve surgical anesthesia with a need for conversion to a general anesthetic for emergency caesarean section has not been described. We conducted a preliminary audit of our clinical practice between January 2019 et July 2019 where 51 patient files were randomly drawn and analyzed. The evaluation was conducted from a prospectively collected database of patient paper records with data collection completed from the electronic medical record software used at the CHU of Bordeaux, Dxcare® (Medasys) [17]. When sodium bicarbonate was added to the mixture through the epidural catheter, there was a decrease of 50% in the time to surgical anesthesia (5 min vs 10 min [*p* < 0.001]), as published in previous studies [13, 14]. Although the sample size is small, in emergency caesarean delivery (fetal extraction in under 15 min), the use of bicarbonate to convert epidural analgesia to surgical anesthesia was associated with a decrease in the incidence of general anesthesia by 80% (4/4 vs 0/7 [*p* = 0.003]).

### Objectives {7}

Based on the results of the preliminary audit, we plan to conduct the QETAL study. This bicentric, randomized controlled patient-blinded clinical trial will focus on parturients who have an epidural catheter in place for labor analgesia and require emergent fetal extraction (<15 min). Our hypothesis is that adding sodium bicarbonate to the lidocaine-epinephrine solution administered through the epidural catheter will reduce the rate of conversion to general anesthesia due to faster onset of surgical epidural anesthesia.

General anesthesia in this context is defined as intravenous induction of general anesthesia and tracheal intubation between the attempted conversion of epidural analgesia to surgical anesthesia via the epidural catheter and umbilical cord clamping. The primary objective is to evaluate whether alkalinization of lidocaine decreases the need for conversion to general anesthesia. Secondary objectives include comparing the delay to maternal incision and fetal extraction, maternal and fetal safety criteria, the level of anesthesia assessed 1 h after surgical incision, and maternal satisfaction with analgesia and anesthesia between the two groups.

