#### Interventions

##### Explanation for the choice of comparators {6b}

This study aims to compare the efficacy and onset time of epidural conversion between lidocaine-epinephrine (group LE) and lidocaine-epinephrine-sodium bicarbonate (group LEB) for emergency caesarean delivery.

In group LE, we will use 20 mL of 2% lidocaine with 1:200,000 epinephrine, which is the current recommendation of the SFAR and considered the gold standard in this circumstance [6].

In group LEB, we will add 2 mL of 4.2% bicarbonate to 10 mL of 2% lidocaine with 1:200,000 epinephrine. This specific mixture and volume have been used at Bordeaux University Hospital since 2016. While the volume of 12 mL may seem small compared to the usual volume used, we have observed in our unit that a volume greater than 12 mL of this solution often leads to nerve block higher than a T4 level. Despite lidocaine being a weak base (pKa=7.9), our preliminary study showed that the commercial preparation of 2% lidocaine with 1:200,000 epinephrine is acidic (pH 4). We conducted hourly measurements of the solution'’ pH over a 24-h period to confirm its stability and suitability for use (Table 1). Alkalinization of lidocaine can modify the non-ionized lidocaine and affect its potency. Moreover, the effectiveness of an injection into the epidural space is heavily influenced by the volume of the injected solution, unlike the intravenous administration route. Therefore, adding 8 mL of sodium chloride to the LEB group to equal the volume of the LE group (20 mL) could potentially result in a significant deviation from the desired level of spinal anesthesia achieved. Such a deviation would be inconsistent with our usual clinical practice, which involves using 12 mL to achieve a T4 level of anesthesia promptly.

**Table 1 Tab1:** Measurements of pH were performed with a pHmeter (Mettler Toledo FiveEasy Plus^TM^ Series, Greifensee, Switzerland, Accuracy 0.01 pH unit) calibrated before each measurement with known solutions of pH 4 and 7

**Time (hour)**	**Solution**	**pH**
T (0)	2% lidocaine with 1:200,000 epinephrine	3.41
T (0)	4.2% *sodium bicarbonate*	7.84
T (0)	2% lidocaine with 1:200,000 epinephrine (10 mL) and 4.2% *sodium bicarbonate* (2 mL)	7.10
T (1)	2% lidocaine with 1:200,000 epinephrine (10 mL) and 4.2% *sodium bicarbonate* (2 mL)	7.10
T (2)	2% lidocaine with 1:200,000 epinephrine (10 mL) and 4.2% *sodium bicarbonate* (2 mL)	7.12

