##### Criteria for discontinuing or modifying allocated interventions {11b}

The experimental procedure in this clinical trial involves injecting a different type and volume of local anesthetic than the control group. This injection is given shortly after the participant’s study inclusion and randomization and is a one-time dose, meaning that the treatment cannot be interrupted. There is no specific experimental protocol to follow after this injection. Instead, the usual medical practices for administering an epidural injection of lidocaine for emergency caesarean section will be followed, and data will be collected.

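### The primary objective credits alkalinization, but the arms also differ in lidocaine dose, epinephrine dose and volume, so only the comparison of the two regimens is identified

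*Protocol article*

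**What the plan says.** The Objectives section {7} names one cause. Its hypothesis is that "adding sodium bicarbonate to the lidocaine-epinephrine solution administered through the epidural catheter will reduce the rate of conversion to general anesthesia", and it continues: "The primary objective is to evaluate whether alkalinization of lidocaine decreases the need for conversion to general anesthesia". The Background paragraph of the Abstract frames the question in the same way, as whether alkalinizing adrenalized lidocaine improves efficacy and onset.

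The comparator section {6b} defines the arms. For control: "In group LE, we will use 20 mL of 2% lidocaine with 1:200,000 epinephrine". For the experimental arm: "In group LEB, we will add 2 mL of 4.2% bicarbonate to 10 mL of 2% lidocaine with 1:200,000 epinephrine".

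The same section says that "the effectiveness of an injection into the epidural space is heavily influenced by the volume of the injected solution". It explains why the volumes were left unequal: "adding 8 mL of sodium chloride to the LEB group to equal the volume of the LE group (20 mL) could potentially result" in a marked departure from the intended level of anesthesia. Section {11b} describes the experimental procedure as "injecting a different type and volume of local anesthetic than the control group". Participant timeline {13} adds that control is given as two 10-mL syringes and LEB as one 12-mL syringe.

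**The concern.** The hypothesis speaks of bicarbonate added to the lidocaine-epinephrine solution. LEB is not the control injection with bicarbonate added. It is half of the control injection with bicarbonate added. The protocol itself treats volume as a strong determinant of the effect, yet the objective mentions neither volume nor dose.

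At stake is what the trial may claim. If the general anesthesia rates differ, the objective invites the statement that alkalinization did it. If they do not, it invites the statement that alkalinization does not help. The contrast that will be estimated contains more than alkalinization, and neither statement follows from it alone.

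**Working it through.** **Inputs.** Arm compositions are from {6b}. Rates of 80% and 40%, two-sided 5% alpha, 90% power and 22 + 44 patients are from Sample size {14}. 2% lidocaine is 20 mg/mL; epinephrine 1:200,000 is 5 micrograms/mL.

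**Step 1: the plan's own figure.** With mean rate (0.8 + 2 × 0.4)/3 = 0.533, pooled variance and no continuity correction:

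n(LE) = {1.960 × √[1.5 × 0.533 × 0.467] + 1.282 × √[0.8 × 0.2 + 0.4 × 0.6/2]}² / 0.4² = (1.198 + 0.678)² / 0.16 ≈ 22.0

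This gives 22 + 44 = 66, as stated. The sample size is not at issue.

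**Step 2: what differs between the arms.**

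| | LE | LEB | LE:LEB |
|---|---|---|---|
| Lidocaine | 20 × 20 = 400 mg | 10 × 20 = 200 mg | 2.0 |
| Epinephrine | 20 × 5 = 100 micrograms | 10 × 5 = 50 micrograms | 2.0 |
| Volume | 20 mL | 10 + 2 = 12 mL | 8 mL more |
| Bicarbonate | none | 2 mL of 4.2% | – |

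**Step 3: what the contrast estimates.** Write p(bicarbonate, size) for the general anesthesia rate, with size meaning the dose-and-volume package. The trial estimates

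p(yes, small) − p(no, large) = [p(yes, small) − p(no, small)] + [p(no, small) − p(no, large)].

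The first bracket is the bicarbonate effect and the second is the dose-and-volume effect. No arm observes p(no, small), so there is one equation with two unknowns. If the trial found exactly the planned difference of −40 points, the bicarbonate effect would be −40 minus the second bracket: −50 points if the smaller package costs LEB 10 points, −30 if it gains 10, and 0 if it gains 40. More patients would sharpen the −40 but not the split.

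**Step 4: illustration of size.** The documents give no dose or volume effect, so the shifts below are assumptions, added to the LEB rate.

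Suppose bicarbonate alone lowers the rate by the planned 40 points:

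| Assumed dose/volume shift | LEB rate | Power with 22 + 44 | N for 90% power |
|---|---|---|---|
| −20 points | 20% | above 0.99 | 30 |
| −10 points | 30% | 0.99 | 42 |
| 0 | 40% | 0.90 | 66 |
| +10 points | 50% | 0.67 | 117 |
| +20 points | 60% | 0.36 | 246 |

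With the +20 shift, a real 40-point bicarbonate effect would be missed with probability 1 − 0.36 = 0.64.

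Now suppose bicarbonate does nothing and the package alone takes LEB to 60% or 40%. An uncorrected chi-squared test, with probabilities summed exactly, would be significant with probability 0.36 or 0.89.

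**The case against.** Much of the protocol already speaks at the level of regimens. The comparator section opens by setting group LE against group LEB, section {11b} discloses that both type and volume differ, the primary analysis in {20a} compares the two groups, and the background {6a} introduces the two solutions as the combinations mainly used in the unit. Alkalinization could be read as shorthand for the LEB mixture. The unequal volume is also argued for, not overlooked. All of this stands. It confines the problem to the wording of the objective, the hypothesis and the matching Abstract text. It does not remove it: the argument in {6b} concerns adding saline to LEB, and no section mentions the halved lidocaine and epinephrine doses as a difference between the arms.

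The second objection is that the smaller regimen works against LEB, so that an LEB advantage would be conservative evidence for bicarbonate. The documents lend this some support: {6b} reports that more than 12 mL of the alkalinized mixture often gives a block above T4, so more volume goes with more spread, and the primary outcome is general anesthesia for insufficient analgesia. Positive and null results are therefore not equally hard to read, and the null result is the weaker one. But the remark concerns block height, not conversion, and carries no effect size. One syringe instead of two could also act the other way where minutes matter; no injection times are given.

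A reader might go further and infer that the protocol announces a conclusion that it cannot support. It does not. The Discussion and the Discussion paragraph of the Abstract say only what alkalinization could or may achieve.

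**Conclusion.** The point holds as a mismatch between the stated objective and the contrast that the arms deliver. Bicarbonate changes together with a two-fold difference in lidocaine and epinephrine dose and an 8-mL difference in volume, so its separate effect is not identified at any sample size. This rests only on the stated compositions. The shifts in the illustration are assumed, and the direction and size of any dose or volume effect are not given in the documents.

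Two stronger readings are tempting and are not supported. One is that the trial itself is invalid: it remains a sound randomized comparison of two complete regimens. The planning rates also seem to suit that comparison, because the audit behind them (4/4 v 0/7) comes from a unit that mainly used these same two mixtures. The other is that a positive result could never count in favour of bicarbonate: it could, given the assumption that less drug and less volume cannot help LEB. That assumption is plausible for volume but unproven.

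**What to change.** Keep the arms, outcome, test and sample size. Reword the primary objective and hypothesis in {7}, and the matching Abstract sentence, to agree with the regimen-level aim in {6b}. For example: *to determine whether epidural conversion with the 12-mL alkalinized lidocaine-epinephrine mixture, compared with the 20-mL lidocaine-epinephrine solution, lowers the rate of conversion to general anesthesia.*

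Add one sentence saying that bicarbonate, lidocaine dose, epinephrine dose and volume change together, and that the effect of bicarbonate alone is not estimated. Word the conclusions of the report in the same way, for a null result as well as a positive one. If a positive result is offered as support for alkalinization, state the assumption about dose and volume beside it. Do not describe both regimens as established practice at both centres, since the protocol documents this for Bordeaux only.

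The cost is a few sentences and a narrower claim: superiority of one regimen over another, not of alkalinization as such.

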### Trial design {8}

This QETAL study is a bicentric patient-blinded, two parallel-arms randomized, controlled, clinical trial of superiority. Patients will be randomly assigned in a 2:1 ratio in group LEB (lidocaine-epinephrine-sodium bicarbonate) and group LE (lidocaine-epinephrine) respectively.

## Methods: participants, interventions, and outcomes

### Study setting {9}

The patients will all be recruited from two academic hospitals, the University Hospital of Bordeaux and the Bayonne Hospital, southwestern France.

### Eligibility criteria {10}

Parturients with the following criteria will be included: adult patients (age ≥ 18 years) who are affiliated with or beneficiary of French government-sponsored health insurance (sécurité sociale), having an initial indication for vaginal delivery, who require emergent fetal extraction via caesarean section (delay < 15 min), who are informed, and who have given their written consent according to the methods described in French Law [18], signed by the participant and the investigating physician at the latest after the therapeutic intervention.

Parturient with one or more of the following criteria will be not included: age less than 18 years, persons placed under guardianship, opposition to participation in the research before caesarean delivery, refusal or inability to consent, lack of understanding or significant language barrier, having another indication for general anesthesia defined by the following situations: non-functional epidural analgesia, consciousness disorders, eclampsia, suspected amniotic embolism, confirmed or suspected severe bleeding before birth, any contraindication to the use of the products defined in the protocol (adrenalized lidocaine; sodium bicarbonate).

### Who will take informed consent? {26a}

When eligibility to participate is validated, written information on the study is given during preoperative anesthesia consultation. In addition, a QRC code is given and video information can be consulted on YouTube (https://www.youtube.com/watch?v=JNabPb1vlRk). Upon the patient’s arrival in the hospital delivery room, the QRC code is displayed and the video can again be consulted. Before placement of the epidural catheter, the investigating physician verifies that the patient has understood the informational leaflet. In the case of emergency caesarean delivery (<15 min), the patient will have provided oral informed consent prior to the injection of either the LEB or LE mixture via the epidural catheter. After the caesarean delivery, informed written consent will be collected in the post-anesthesia care unit by the managing anesthesiologist.

### Additional consent provisions for collection and use of participant data and biological specimens {26b}

Not applicable. No biological samples and no additional consent provisions will be collected.

#### Interventions

##### Explanation for the choice of comparators {6b}

This study aims to compare the efficacy and onset time of epidural conversion between lidocaine-epinephrine (group LE) and lidocaine-epinephrine-sodium bicarbonate (group LEB) for emergency caesarean delivery.

In group LE, we will use 20 mL of 2% lidocaine with 1:200,000 epinephrine, which is the current recommendation of the SFAR and considered the gold standard in this circumstance [6].

In group LEB, we will add 2 mL of 4.2% bicarbonate to 10 mL of 2% lidocaine with 1:200,000 epinephrine. This specific mixture and volume have been used at Bordeaux University Hospital since 2016. While the volume of 12 mL may seem small compared to the usual volume used, we have observed in our unit that a volume greater than 12 mL of this solution often leads to nerve block higher than a T4 level. Despite lidocaine being a weak base (pKa=7.9), our preliminary study showed that the commercial preparation of 2% lidocaine with 1:200,000 epinephrine is acidic (pH 4). We conducted hourly measurements of the solution'’ pH over a 24-h period to confirm its stability and suitability for use (Table 1). Alkalinization of lidocaine can modify the non-ionized lidocaine and affect its potency. Moreover, the effectiveness of an injection into the epidural space is heavily influenced by the volume of the injected solution, unlike the intravenous administration route. Therefore, adding 8 mL of sodium chloride to the LEB group to equal the volume of the LE group (20 mL) could potentially result in a significant deviation from the desired level of spinal anesthesia achieved. Such a deviation would be inconsistent with our usual clinical practice, which involves using 12 mL to achieve a T4 level of anesthesia promptly.

**Table 1 Tab1:** Measurements of pH were performed with a pHmeter (Mettler Toledo FiveEasy Plus^TM^ Series, Greifensee, Switzerland, Accuracy 0.01 pH unit) calibrated before each measurement with known solutions of pH 4 and 7

**Time (hour)**	**Solution**	**pH**
T (0)	2% lidocaine with 1:200,000 epinephrine	3.41
T (0)	4.2% *sodium bicarbonate*	7.84
T (0)	2% lidocaine with 1:200,000 epinephrine (10 mL) and 4.2% *sodium bicarbonate* (2 mL)	7.10
T (1)	2% lidocaine with 1:200,000 epinephrine (10 mL) and 4.2% *sodium bicarbonate* (2 mL)	7.10
T (2)	2% lidocaine with 1:200,000 epinephrine (10 mL) and 4.2% *sodium bicarbonate* (2 mL)	7.12
T (3)	2% lidocaine with 1:200,000 epinephrine (10 mL) and 4.2% *sodium bicarbonate* (2 mL)	7.12
T (4)	2% lidocaine with 1:200,000 epinephrine (10 mL) and 4.2% *sodium bicarbonate* (2 mL)	7.08
T (5)	2% lidocaine with 1:200,000 epinephrine (10 mL) and 4.2% *sodium bicarbonate* (2 mL)	7.14
T (6)	2% lidocaine with 1:200,000 epinephrine (10 mL) and 4.2% *sodium bicarbonate* (2 mL)	7.08
T (7)	2% lidocaine with 1:200,000 epinephrine (10 mL) and 4.2% *sodium bicarbonate* (2 mL)	7.05
T (8)	2% lidocaine with 1:200,000 epinephrine (10 mL) and 4.2% *sodium bicarbonate* (2 mL)	7.06
T (9)	2% lidocaine with 1:200,000 epinephrine (10 mL) and 4.2% *sodium bicarbonate* (2 mL)	7.06
T (10)	2% lidocaine with 1:200,000 epinephrine (10 mL) and 4.2% *sodium bicarbonate* (2 mL)	7.04
T (11)	2% lidocaine with 1:200,000 epinephrine (10 mL) and 4.2% *sodium bicarbonate* (2 mL)	7.06
T (12)	2% lidocaine with 1:200,000 epinephrine (10 mL) and 4.2% *sodium bicarbonate* (2 mL)	7.10
T (24)	2% lidocaine with 1:200,000 epinephrine (10 mL) and 4.2% *sodium bicarbonate* (2 mL)	7.08

